### Randomization

Schools from each of the participating municipalities registered in the INEP’s national registry of schools will be randomly selected. The schools must meet the following inclusion criteria: (a) a public school and (b) have at least three 8th grade classes. Thirty schools will be drawn in Fortaleza, 30 schools in São Paulo and 10 schools in Eusébio. Among the schools selected to participate in the study, a second random draw will define which schools will be included in the control group and which will be included in the experimental group, maintaining a ratio of 1:1 in the number of control and experimental schools in each municipality. After selecting the schools, a list with the names of the selected schools will be forwarded to each education department of the participating municipalities to request authorization for participation in the study. Due to the involvement of the government, all schools typically agree to participate, as occurred in a previous study [16].

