### Study design

A randomized controlled trial with two parallel groups (intervention and control) will be conducted to evaluate the effectiveness of the program for adolescents enrolled in 8th grade middle school in 70 public schools in three Brazilian cities, totaling approximately 6300 students distributed in 210 groups. Randomization will be conducted at the school level. Schools randomly selected to be part of the intervention group will offer the 12 lesson #Tamojunto2.0 program in the year 2019. Schools in the control group will not offer prevention programs or activities in 2019. The selection of schools and the allocation to the control or intervention group will be performed by a simple random draw from the list of the National Institute for Educational Studies and Research ‘Anísio Teixeira’ (INEP), which includes all schools from each municipality.

The baseline data (T1) will be collected two weeks before implementation of the program in February/March 2019, and the follow-up data will be collected at 9 months (T2) in November/December 2019 and at 18 months (T3), August/September 2020 after the initial data collection in August 2020. The data will be collected simultaneously for both groups. This protocol was prepared in accordance with SPIRIT 2013 [22], and the study will be conducted according to the CONSORT guidelines [23].

At the end of each lesson, all teachers in the experimental classes will complete a fidelity and dose form, stating which of the planned activities were or were not taught in the lesson and if the teacher made any changes. Figure 1 shows the study design flowchart.

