### Data analysis of the randomized controlled trial

The data will initially be analyzed by a descriptive analysis, that is, qualitative variables will be summarized as numbers and percentages and numerical variables as means, standard deviations, medians, minima and maxima. Descriptive analyses will be performed for different patterns of drug use. This dataset will be used to calculate sample weights through the svy command in Stata so that the baseline data analysis can be presented in an expanded form, aiming at correcting for losses and extrapolating the data to the sample universe [39, 40].

All analyses will be carried out in the two samples: “intention to treat” (ITT), which will include all the participating classes that received at least one lesson of the program, and “per protocol” (PP). The PP analysis will include only those classes that receive the complete protocol (12 lessons), determined based on evaluating the dose and fidelity form that will be completed by the teacher at the end of each lesson.

Because the data are collected in groups, they are not independent at two levels (school and class), and the measures of association should be analyzed through GLLAMM (Generalized Linear Latent and Mixed Models), which calculates the level of dependence between the data [41]. Due to the hierarchical structure of the data, multilevel models will be used to simultaneously test for differences in the prevalence of outcomes between times and between groups, considering schools as a modeling level (Gllamm Stata 14). All analyses will be adjusted by sex, socioeconomic level and site. The analyses will be performed in Stata 15 (descriptive analyses and multilevel GLLAMM), and a significance level of 5% will be adopted.

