## Trial status

By the time of this submission (February/2019), the study is in the recruitment and agreement phase with the selected schools.

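### As sequenced, schools appear to be allocated to arms before authorisation is requested, and nothing says that arm is withheld when it is

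*Protocol article*

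**What the plan says.** The Study design section makes the school the unit: "Randomization will be conducted at the school level". The Randomization section then sets out these steps, in this order:

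1. A sampling draw from the national school registry: "Thirty schools will be drawn in Fortaleza, 30 schools in São Paulo and 10 schools in Eusébio".
2. An allocation draw, 1:1 within each municipality: "Among the schools selected to participate in the study, a second random draw will define which schools will be included in the control group". The remaining schools form the experimental arm.
3. The request for permission: "After selecting the schools, a list with the names of the selected schools will be forwarded to each education department of the participating municipalities".
4. An expectation that, with government involved, schools typically agree, as they did in an earlier study.

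The Trial status section reports that in February 2019 "the study is in the recruitment and agreement phase with the selected schools". Baseline collection was due in February/March 2019 (Study design).

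The article does not say whether arm is known when agreement is sought, and it gives no rule for a school that declines.

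**The concern.** In a trial of 70 schools, the random draw is what makes the two groups of 35 comparable. If a school can decline after its arm is fixed and known, the schools that remain are no longer simply the randomised ones.

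The two arms ask for different things. An experimental school must release one teacher per class for a 16-hour training course, deliver 12 lessons and receive two on-site visits (Intervention). A control school must run no prevention programmes or activities in 2019 (Study design). Willingness to take part could therefore differ by arm, and schools that decline could differ in their level of drug use. The planned adjustment for sex, socioeconomic level and site would not necessarily remove such a difference.

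**Working it through.** **Order of the steps.** The allocation draw is described before the request for authorisation, and that request is introduced as following the selection of schools. School-level agreement is a real step: the Randomization section speaks of schools agreeing, and the Trial status section of an agreement phase with them. Neither section places allocation after agreement.

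**Inputs (Sample size calculation section).** 35 schools per arm, at least 90 students per school, binge drinking in the past month at 10%, difference 2.5 points (taken as 10% against 7.5%), ICC 0.005, significance level 5% (taken as two-sided), stated power 82%.

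**The plan's own figure.**
- Design effect = 1 + (90 − 1) × 0.005 = 1.445.
- Effective n per arm = 3150 / 1.445 = 2179.9.
- SE = √[(0.10 × 0.90 + 0.075 × 0.925) / 2179.9] = 0.00855.
- 0.025 / 0.00855 = 2.92, which gives power 83.2% by the normal test and 82.2% by a t test on 68 degrees of freedom (70 schools less 2).

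The stated 82% is reproduced. No sample-size figure is in question.

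**How far schools plausibly differ.** The stated ICC implies a between-school variance of 0.005 × 0.10 × 0.90 = 0.00045, so a between-school SD of √0.00045 = 0.0212, or about 2.1 points.

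**Shift from refusals (number and prevalence of refusers are assumptions).** If r of 35 schools leave one arm, and their prevalence is d points above average, the mean of the remaining schools falls by r × d / (35 − r). The last column is the two-sided rejection rate when there is no true effect.

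| Schools refusing in one arm | Shift with d = 2.12 (1 SD) | Share of 2.5 points | False-positive rate |
|---|---|---|---|
| 0 | 0 | 0% | 5.0% |
| 1 | 2.12 / 34 = 0.06 | 2% | 5.1% |
| 3 | 3 × 2.12 / 32 = 0.20 | 8% | 5.5% |
| 5 | 5 × 2.12 / 30 = 0.35 | 14% | 6.6% |

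Refusal of higher-prevalence schools in the experimental arm would favour the program. In the control arm it would count against the program.

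**Power.** With 3 or 5 experimental schools lost and not replaced, the t-test power falls from 82.2% to 80.6% or 79.4%. This loss is minor; the issue is bias.

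**The case against.** The strongest case on the other side has five parts.

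- **The order is implied, not stated.** The Randomization section also uses the idea of selection for the first draw, so the list could be sent after sampling and before allocation. It is said to carry school names; arms are not mentioned. The agreement phase in the Trial status section does not date the second draw. This stands, so the point is that allocation appears to come first.
- **Refusals are expected to be about nil.** The Randomization section says so, and the Participants section adds that the cities were chosen because collaboration on this program already existed. A reader might infer that refusals do happen and differ by arm; the documents do not support that. But the expectation rests on past experience and is not a design safeguard.
- **The request goes to education departments.** A department that declined outright would remove both arms of its municipality equally. This is true, but schools also agree individually, so refusal by single schools remains possible.
- **Larger shifts are tempting but strained.** Refusers 5 points above average would give 3 × 5 / 32 = 0.47 or 5 × 5 / 30 = 0.83 points. Under the stated ICC, such schools lie 5 / 2.12 = 2.4 SDs above the mean, which is too extreme to assume for three or five refusers in one arm.
- **The analysis set does not decide the matter.** The intention-to-treat set is defined as one "which will include all the participating classes that received at least one lesson of the program". A reader might infer that a stricter definition would protect against refusals. It would not: a school that declines supplies no questionnaires, and no definition recovers outcomes never collected. That definition is a separate question.

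**Conclusion.** The concern holds in a limited form. The text, read in sequence, puts allocation before the request for authorisation and does not say that arm is concealed at that stage. Any refusal would then fall after randomisation and could depend on arm.

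The likely size is small: about 0.20 or 0.35 points for 3 or 5 refusals in one arm, and nil with none. These figures rest on assumed refusal counts, on refusers one between-school SD above average, and on the protocol's ICC of 0.005. The documents do not show that refusals occurred, that arms were disclosed, or that any stated number is wrong. The change is worth making because it removes a possible selection bias at almost no cost.

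**What to change.** In the Randomization section, state the order explicitly:

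1. Draw the 70 schools.
2. Obtain education-department authorisation and school agreement without disclosing arm.
3. Only then make the 1:1 draw within each municipality.

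If allocation has already been drawn, say so, do not replace schools that decline, and report refusals by allocated arm.

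This needs no extra schools or staff. The cost is less lead time between allocation and teacher training, which matters because agreement was still being sought in February 2019, with baseline due in February/March.

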### Instrument

The instrument to be used for data collection in evaluating the program effectiveness was designed using instruments previously used in studies evaluating the effect of drug prevention programs both in Brazil [16, 25] and abroad [14]. One of the instruments used as a base was created by the EU-DAP (European Drug Addiction Prevention Trial) and used in a previous effectiveness evaluation of Unplugged [26]. In Brazil, this instrument has been translated and adapted into Portuguese [27], with some questions replaced by questions adopted from two questionnaires widely used in several studies among Brazilian students: the World Health Organization questionnaire used in the VI Brazilian Survey of Drug Use among Students [28] and the National Survey of School Health questionnaire used by the Ministry of Health [5]. Details of the instrument are presented in Table 1.

**Table 1 Tab1:** Details of the instrument to be applied among the students at the evaluation time points

Variable	Main Use *	Source	Scale
Drug use in lifetime (first use, incidence and prevalence), past year and past month (prevalence)	Primary outcomes (alcohol, tobacco, marijuana, inhalant, cocaine, crack and amphetamine use and binge drinking)	CEBRID [28]	22 dichotomous questions
Socioeconomic class	Confounder	ABEP [35]	A scale with 15 items
Demographic data	Confounders	CEBRID [28]	2 questions (age and sex)
Decision-making	Mediator	EUDAP [26]	A scale with 9 dichotomous items
Positive and negative beliefs	Mediator		Two scales with 11 dichotomous items each (one for alcohol and one for marijuana)
Normative beliefs	Mediator		Two scales: a Likert scale with 4 items and a dichotomous scale with 11 items
Knowledge about drugs	Mediator		A scale with six items
Refusal skill	Mediator		A scale with three items
School violence	Secondary outcome	Olweus Bully Victim Questionnaire [30]	Two scales: a scale to measure violence perpetrated with eight dichotomous items each and a scale to measure violence suffered with seven dichotomous items each
Psychiatric symptoms	Secondary outcome	Strengths and Difficulties Questionnaire [31]	A scale with 25 dichotomous items
Eating disorders	Secondary outcome	SCOFF [33]	A scale with 5 dichotomous items

The form that evaluates dose and fidelity (Table 2), to be completed at the end of each lesson by the experimental group teachers, was prepared based on the EUDAP instrument [29].

**Table 2 Tab2:** Instrument for evaluating the #Tamojunto2.0 program implementation dose and fidelity

Instrument	Completion	Goals	Content
Forms for monitoring the application of the #Tamojunto2.0 lesson-by-lesson. Teacher.	To be completed after each of the 12 program lessons by the teachers who will implement the program.	Assess the dose of program activities being provided by teachers to students and whether the teacher is following the original lesson plan of the program.	▪ The teacher will complete the form at the end of each class, reporting which of the activities planned for that lesson (as stated in the student and teacher handbooks) were actually fully taught to the students and whether any changes were made to the lessons.

To match the questionnaires across the evaluation time points, students will fill out a secret code on the first page of the questionnaire that involves generating letters and numbers from personal information. In this way, the codes can only be decoded by the students themselves. The codes allow the researchers to match individual questionnaires from different evaluation time points while providing the anonymity and confidentiality essential for a study of illicit behavior [36]. The databases of the two evaluation time points will be integrated by matching the secret codes using the Levenshtein algorithm, which can identify similarities between a set of characteristics [37].

### Primary outcomes

The primary outcomes will be assessed through dichotomous questions about use in the last 30 days (yes/no), in the last 12 months (yes/no), and prior to the study period (incidence = new cases) of the drugs alcohol, tobacco, marijuana, inhalants, cocaine, crack and amphetamines and binge drinking.

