## Methods

### Aims

The main objective of the study is to evaluate the effectiveness of the school-based program #Tamojunto2.0 at 9 and 18 months of follow-up in the prevention of drug use (alcohol, tobacco, inhalants, marijuana, cocaine, crack and amphetamines) and binge drinking among Brazilian students. Our main hypothesis is that the #Tamojunto2.0 program will delay the first use of these drugs and will decrease the prevalence of use among students who participate in the intervention compared to the students in the control group.

The second objective of this study is to evaluate the effectiveness of the program at 9 and 18 months of follow-up in the prevention of school violence and psychiatric symptoms (depression, anxiety, *attention-deficit/hyperactivity disorder* and eating disorders) among Brazilian students. Our second hypothesis is that the #Tamojunto2.0 program will reduce the prevalence and incidence of secondary outcomes among students participating in the intervention compared to the students in the control group.

The third objective of the study is to evaluate the mediating effect of the skills taught by the program (decision-making skills, refusal skills, knowledge about drugs and beliefs about drugs) in reducing primary outcomes (alcohol, tobacco, marijuana, inhalant, cocaine, crack and amphetamine use and binge drinking) and secondary outcomes (reports of school violence and psychiatric symptoms), comparing the control and intervention groups at three different time points (0, 9 and 18 months). Our third hypothesis is that the improvement in the skills taught by the program will mediate the program’s effect on reducing the primary and secondary outcomes, as described by a logical model.

Finally, the fourth objective of the present study is to evaluate the program implementation fidelity to identify possible changes in the original content and to measure if the dose of the program offered to the students influences the effects of the program. Our fourth hypothesis is that the greater the dose of the program offered to the students and the smaller the changes to the original content are, the greater the effect of the program in the prevention of the proposed outcomes will be.

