### Sample size calculation

The PASS 15.0 software was used to calculate the sample sizes of the two intervention groups in a cluster randomized design [24]. A sample size of at least 3150 adolescents in the control group and 3150 in the intervention group, distributed among 35 clusters (schools) with at least 90 subjects in each arm, will reach a power of 82% in identifying a difference between groups of 2.5% for the outcome of binge drinking in the past month, with an initial prevalence of 10%, a significance level of 5%, and an intraclass correlation of 0.005. Thus, it is necessary to ensure the inclusion of at least three 8th grade classes from each sampled school, with 35 schools in the intervention group and 35 in the control group. Therefore, 70 schools will be selected to ensure a minimum sample size of 6300 adolescents, considering possible losses to follow-up.

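### Every drug, time window and follow-up is primary at 5% with no ranking, and the one powered outcome, past-month binge drinking, is never made the primary test

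*Protocol article*

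**What the plan says.** All references are to the protocol article.

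- **Primary outcomes** lists three measures, "use in the last 30 days (yes/no), in the last 12 months (yes/no), and prior to the study period (incidence = new cases"), each "of the drugs alcohol, tobacco, marijuana, inhalants, cocaine, crack and amphetamines and binge drinking". No behaviour or window is placed first.
- **Instrument, Table 1** labels the same set as primary outcomes and counts "22 dichotomous questions".
- **Aims** sets the main objective "at 9 and 18 months of follow-up in the prevention of drug use (alcohol, tobacco, inhalants, marijuana, cocaine, crack and amphetamines) and binge drinking". Neither follow-up is named as the main one.
- **Data analysis of the randomized controlled trial** uses multilevel models that test time and group together, repeats all analyses in an intention-to-treat and a per-protocol sample, and states that "a significance level of 5% will be adopted". It gives no division of that level and no order of testing.
- **Sample size calculation** rests on one member of the family, a "difference between groups of 2.5% for the outcome of binge drinking in the past month", with 82% power. It does not say at which follow-up.
- The structural equation paragraph of the data analysis section remarks that latent transition analysis has a lower false discovery rate than multilevel logistic models when there are multiple outcomes.

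**The concern.** The trial is meant to inform whether the programme is expanded as public policy (Abstract, Discussion; Conclusion). With a large unranked primary family, the plan does not say which result answers that question. Suppose alcohol initiation came out worse and inhalant use better, each at p below 0.05. Both would be primary findings, and nothing in the article says which one decides. The earlier trial makes this concrete: Background reports a 30% higher risk of first alcohol use at 9 months and 13% at 21 months in the intervention group. Strengths and limitations calls it important to learn whether the revised alcohol lesson removes that effect. Alcohol initiation is nevertheless one entry in the list.

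The remark on latent transition analysis does not help. It concerns a separate analysis, and the models it calls more prone to false discovery are the type used for the primary outcomes.

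**Working it through.** **1. The plan's own power figure.** Inputs from Sample size calculation: 35 schools per arm, 90 students per school, 3150 students per arm, 10% prevalence, 2.5-point difference, intraclass correlation 0.005, 5% level (two-sided assumed).

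- Design effect = 1 + (90 − 1) × 0.005 = 1.445.
- Effective size = 3150 / 1.445 = 2180 per arm.
- Power for 10% against 7.5%: pooled standard error = √(2 × 0.0875 × 0.9125 / 2180) = 0.00856. Unpooled standard error = √((0.10 × 0.90 + 0.075 × 0.925) / 2180) = 0.00855. Then Φ((0.025 − 1.96 × 0.00856) / 0.00855) = 83.2%. A continuity correction gives 81.8%, and a t reference with 68 degrees of freedom gives 82.2%.

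The stated 82% reproduces, but only for one test at the full 5%.

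**2. Number of primary tests (intention-to-treat set).**

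- Primary outcomes section: 8 behaviours × 3 measures = 24 outcomes. Table 1: 22 items. One breakdown that gives 22 is 7 drugs × 3 windows + 1 binge item; this is an assumption, as the article gives none.
- One joint time-by-group test per outcome: 22 to 24 tests.
- One test at each of two follow-ups: 22 × 2 = 44 to 24 × 2 = 48 tests.

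**3. False positives if the programme has no effect.** For k independent tests at 5%, the chance of at least one is 1 − 0.95^k. For correlated tests, equicorrelated normal statistics were simulated (at least 100,000 draws per case).

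| Correlation | 22–24 tests | 44–48 tests |
|---|---|---|
| 0 | 68–71% | 90–91% |
| 0.5 | 44–46% | 59–61% |
| 0.7 | 30–31% | 39–40% |
| 0.9 | about 16% | about 19% |

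The expected number of false positives is 0.05k: 1.1–1.2 for 22–24 tests and 2.2–2.4 for 44–48. It does not depend on the correlation.

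Counting only false claims of benefit (2.5% per test), independence gives 1 − 0.975^k = 43–46% for 22–24 tests and 67–70% for 44–48.

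**4. What keeping the whole family would cost.** Power for binge drinking (10% against 7.5%) by the formula in step 1, under Bonferroni:

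- One test at 0.05: 83.2%.
- Both follow-ups at 0.025 each: 75.2%.
- 44 tests at 0.05/44 = 0.00114: 36.9%.
- 48 tests at 0.05/48 = 0.00104: 36.0%.

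**The case against.** **The count is not stated in the article.** This stands. The models test times and groups simultaneously, which can be read as one joint test per outcome, hence 22–24. But Aims asks for effectiveness "at 9 and 18 months of follow-up in the prevention of drug use", which points to a test at each follow-up. Both counts are therefore carried through.

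**Independence is implausible.** This also stands. A reader might infer that a programme with no effect would give a significant primary result about nine times in ten. The documents do not support that. The data analysis section itself cites high correlation between the drugs used. The outcomes also overlap: 30-day use implies 12-month use, binge drinking implies alcohol use, and the same students are measured twice. The 90–91% is an upper end, and with 44–48 tests the chance falls to about one half near correlation 0.6.

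**The statistical analysis plan may settle it.** This stands in part. The plan is not shown, so a reader should not infer that no adjustment or testing order exists anywhere. But which outcomes are primary is fixed in this article. A later plan that chose one would depart from Aims, Table 1 and Primary outcomes. Bonferroni across the 44–48 tests would leave binge drinking with about 36–37% power.

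**Binge drinking and alcohol initiation are not ignored.** True: one drives the sample size and the other the rationale. Neither fact gives either outcome priority in the primary analysis.

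**Conclusion.** The concern holds as a fault in what the article fixes: an unranked primary family of 22–24 or 44–48 tests at an undivided 5%, with power worked out for one outcome that is never singled out as the primary test.

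Its size cannot be pinned to one figure. Across both counts and correlations from 0 to 0.9, the chance of at least one false-positive primary result runs from about 16% to 91%, and 1.1–2.4 false positives are expected whatever the correlation. This assumes two-sided tests, a programme with no effect, equal correlation between tests and the intention-to-treat set alone. Even the lowest value is about three times the nominal 5%.

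A reader might also infer that the sample size is wrong. It is not: the 82% reproduces, on the condition that past-month binge drinking at one follow-up is tested at the full 5%.

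**What to change.** Before outcome data are analysed:

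1. Name past-month binge drinking at one stated follow-up as the single primary outcome, tested at two-sided 5%. Whether that is 9 or 18 months is for the investigators to choose and state. The article gives no attrition figures that would decide it.
2. Name alcohol initiation among baseline never-users, the harm signal from the earlier trial, as key secondary. Test it next in fixed sequence, at two-sided 5%, only if the primary test is significant. Report its estimate and confidence interval in either case.
3. Report the remaining drug, window and follow-up combinations as secondary with false discovery rate control, or as exploratory with confidence intervals.

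The cost is wording. No schools, students or measurements are added, and the stated 82% power is kept for the primary outcome. Baseline collection was due in February/March 2019 and the article was submitted in February 2019, so the workable deadline is before outcome analysis rather than before data collection. The downside is small: isolated findings for other substances lose confirmatory status.
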